### Sample size

The standard approach to sample size calculation is to aim to detect a worthwhile intervention effect. This is difficult here because there is a linear relation between overweight and mortality (30 % increase per 5 kg/m [2]) [19]. This kind of intervention may be applied broadly in contexts outside of the specific behavioural intervention we propose here and in any case, even here, at its likely maximal intensity and cost, is likely to cost around £20 per person or less in public health practice. Even very small decrements in weight are likely to be cost effective if they are maintained throughout life. Consequently, instead of an approach where we specify a sample size based on a clinically important difference, we propose a sample size based on the likely size of effect we expect to achieve, a 2 kg difference in change in weight at 12 months. A total of 280 participants randomised to each group (n = 560) will be sufficient to detect a 2 kg difference in change in weight at 12 months follow-up between the intervention and comparator group, with 90 % power and 5 % significance level. This estimate is based on data from our pilot trial [13] where we found the standard deviation of the difference from baseline (i.e., end of weight loss/start of maintenance programmes) to nine months follow-up in those who lost at least 5 % of their starting weight was 6.3 kg. 560 participants allows for 25 % loss to follow-up at 12 months.

### Randomisation

The randomisation list will be developed by an independent statistician within the Primary Care Clinical Research and Trials Unit using NQuery Advisor. Participants will be randomised to the intervention or comparator groups on a 1:1 basis using random permuted blocks of varying size. Some people who have lost weight will want to continue attending the weight management group and pay themselves, after completing the NHS-provided 12 week course, and this is likely to have an important effect on weight at 12 months. To ensure this effect is balanced by treatment arm we will stratify randomisation by whether participants intend to continue with their weight loss programme or not.

Participants will be randomised at the baseline appointment after consent is gained and eligibility checked. The research assistants will be operating in participants’ homes and out of office hours so the only option available will be to implement randomisation by opaque sealed envelopes. These will be sequentially numbered and research assistants open these in sequence and the trial manager checks their adherence to this instruction regularly.

### Blinding

In the information sheet participants will not be told that this is a trial about target setting and daily weighing and will therefore be blinded to group allocation. Instead they will be told that it is a trial of different strategies to prevent weight regain after weight loss. After randomisation the intervention group will know they have been allocated to the weighing group as they will receive a set of weighing scales but the comparator group will remain blinded that the intervention group are being asked to weigh themselves daily. We will also ensure researchers taking follow-up outcome measures will be blinded to group allocation by providing the trial documents in a sealed envelope with a sticker on the front to record the weight of the participant prior to asking questions specific to their trial arm, which inevitably would reveal the random allocation. The researcher undertaking weight measurements (primary outcome) will not have collected baseline or three month measurements therefore remain blind to group allocation. Participants will be asked not to reveal their group allocation to researchers at follow-up. The trial statistician will remain blinded to group allocation until analysis is completed.

### Analysis plan

The analyses will be conducted using the intention to treat principle. The primary outcome will be assessed by analysis of covariance to compare weight change (baseline to 12 months) between the groups. Thus the analysis uses weight at follow-up adjusted for baseline weight and adjusts for the baseline stratification factor, intention to maintain or continue weight loss, as is standard. All participants will be included in the primary analysis but those who are absent from follow-up will have final weight imputed. A similar analysis will be used to compare the secondary outcome of change in weight from baseline to three month follow-up.

The analysis of the proportion of participants in each group who regain no more than 1 kg from their weight at the end of the weight loss programme (i.e., successful maintainers) at three and 12 months follow-up will be conducted using generalised mixed modelling adjusting for the stratification variable. The results will be presented as odds ratios, 95 % confidence intervals and associated p values.

We have four pre-planned exploratory subgroup analyses, examining the effect of gender, initial weight loss programme, whether a person is intending to continue to attend their weight loss programme or not and whether a participant wished to lose or maintain weight. It is possible that different weight loss programmes teach people weight loss maintenance skills to a greater or lesser extent and therefore this could modify the effectiveness of the intervention. Gender may also influence the effectiveness of the intervention as previous research has found men lose more weight than females and have had less attempts at weight loss which could influence subsequent maintenance of weight loss [13, 23]. As some participants will wish to continue to lose weight or continue to attend their weight loss programme the intervention we propose here may not be as effective for those that are aiming to lose weight, we will explore whether there is support for this hypothesis.

The effects of the intervention on uncontrolled eating, emotional eating and weight preoccupation at three and 12 months will be investigated. Groups will be compared with repeated measures mixed modelling, adjusting for stratification variable. The results will be summarised as adjusted means and 95 % confidence intervals.

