### Setting and recruitment

All participants in a Public Health funded weight management service will be sent an invitation letter from their service on behalf of the research team, as well as an information leaflet, when they reach week nine of their weight loss programme. The letter will inform participants about this weight loss maintenance study (called LIMIT) and will notify them that as part of the routine service they will be asked whether they are willing to take part in a study to prevent them regaining the weight they may have recently lost. At week 11 of the weight loss programme participants will be asked to report their current weight to enable the research team to calculate the total amount of weight loss since starting their weight loss programme. Those who have lost at least 5 % of their starting weight will be asked by members of the research team to participate in a study about preventing weight regain. Figure 1 depicts participant flow through the trial.

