### Inclusion criteria

Aged 18 years or more.Own a mobile phone or landline phone that can receive SMS text messages.Able to understand English sufficiently to complete the study procedures.People who have lost at least 5 % of their starting weight at the end of their weight loss programme. The initial screen for 5 % weight loss is based on self-reported weight at the baseline screening call and is later verified objectively at the baseline home visit. Because we anticipate there is likely to be variation in participants self-reported weight using their home scales and the calibrated scales used by researchers at the home visit to verify percentage weight loss, the decision was made to allow some flexibility in the inclusion criteria at the home visit and include people who were confirmed to have lost at least 4 %.

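### The primary ANCOVA is valid but could also adjust for starting weight and gender, already held for every participant, for a small gain in precision of unknown size

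*Protocol article*

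**What the plan says.** The primary outcome is the difference between groups in weight change from baseline to 12 months. The Analysis plan assigns it to analysis of covariance and states the covariates: "Thus the analysis uses weight at follow-up adjusted for baseline weight and adjusts for the baseline stratification factor". It describes that factor as "intention to maintain or continue weight loss, as is standard". A similar analysis is planned at three months.

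Other baseline information is held before randomisation:

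- **Amount lost in the programme.** Under Setting and recruitment, participants report their weight at week 11 so that the team can "calculate the total amount of weight loss since starting their weight loss programme". Under Inclusion criteria, the 5% loss "is later verified objectively at the baseline home visit", with 4% accepted at that visit. The starting weight must therefore be on file for everyone randomised.
- **Gender and programme attended.** Both are named for subgroup use: "We have four pre-planned exploratory subgroup analyses, examining the effect of gender, initial weight loss programme". On gender, the article notes earlier research that "men lose more weight than females and have had less attempts at weight loss which could influence subsequent maintenance of weight loss". On programme, the reason given is that programmes may teach maintenance skills to differing extents, which could change how well the intervention works.

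Under Randomisation, the stratification factor is worded differently from the Analysis plan: "we will stratify randomisation by whether participants intend to continue with their weight loss programme or not".

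**The concern.** Baseline weight is the weight after the programme. Within an arm and stratum, the planned model therefore gives two people of equal baseline weight the same expected 12-month weight, even if one has just lost 5% and the other 12%. In a trial about regaining lost weight, the amount lost is an obvious candidate predictor. Gender is a second one, since the article itself links it to later maintenance.

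What is at stake is precision. The planning SD of change is 6.3 kg, against a target difference of 2 kg. The Sample size section also says that even very small weight differences are likely to be cost effective, so the trial has an interest in effects below its target. In a linear model, pre-specified baseline covariates leave the estimated quantity unchanged and narrow its interval if they are prognostic.

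**Working it through.** **Inputs (Sample size and Randomisation sections).** Difference 2 kg; SD of change 6.3 kg (pilot, nine months, those who lost at least 5%); power 90%; significance level 5%; 1:1 allocation; 25% loss to follow-up; 280 per arm. Sidedness is not stated. A two-sided test reproduces the figure, whereas a one-sided test would need only 170 per arm before loss.

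**Step 1: reproduce the plan's figure.**

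n per arm = 2 × (1.96 + 1.2816)² × 6.3² / 2² = 208.5, so 209. Then 209 / 0.75 = 278.7, so 279 per arm and 558 in total. With the t distribution, n is 210 per arm, and 210 / 0.75 = 280, giving 560 exactly. The stated size is confirmed. It uses the SD of change with no allowance for covariates, so the planned power does not depend on any further adjustment.

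**Step 2: reference standard error.** With 210 completers per arm, SE = 6.3 × √(2/210) = 0.615 kg. This is the change-score SE implied by the planning SD. The SE of the planned ANCOVA would already be lower by whatever baseline weight and the stratum explain, which the article does not report. It serves here as a scale for the relative gain.

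**Step 3: effect of added covariates.** Let R² be the share of residual variance that the added covariates explain. The SD becomes 6.3 × √(1 − R²), and power = Φ(difference / SE − 1.96). R² is an assumption.

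| Assumed R² | SE (kg) | Fall in SE | 95% CI half-width (kg) | Power at 2 kg | Power at 1.5 kg |
|---|---|---|---|---|---|
| 0 | 0.615 | – | 1.205 | 90.2% | 68.4% |
| 0.02 | 0.609 | 1.0% | 1.193 | 90.8% | 69.3% |
| 0.05 | 0.599 | 2.5% | 1.175 | 91.6% | 70.6% |
| 0.10 | 0.583 | 5.1% | 1.143 | 92.9% | 73.0% |

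The fall in SE is 1 − √(1 − R²), so it applies whatever the starting SE. The power columns start from the change-score SE and are indicative only.

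**Step 4: the adjustment factor.** Randomisation stratifies on intending to continue with the programme. The Analysis plan labels the factor as an intention to maintain or continue weight loss. The same section lists intention to keep attending and the wish to lose or maintain weight as two separate subgroup variables. A person could wish to lose more weight without intending to stay in the programme, so the labels are not interchangeable. Any revised model has to say which one is meant.

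**The case against.** The strongest reply is that nothing here is wrong. ANCOVA on baseline weight and the stratification factor is a sound primary analysis, and the sample size delivers its power without help from covariates. The plan also already adjusts for the stratification factor, and intended continuation is the one variable it expects to matter greatly for 12-month weight. All of this stands.

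It also stands that the gain is not documented. No R² or correlation is given for any of these variables, and no statement says that the amount lost predicts regain. That premise is a reasonable expectation, not something taken from the protocol. At R² = 0.02 the gain is negligible.

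Two stronger readings are tempting, and the article does not support them:

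- A reader might infer that the plan also identifies the programme attended as prognostic. Its stated argument is effect modification, which the subgroup analysis addresses. The mechanism might affect regain in the comparator arm too, but the article does not say so. Nor does it give the number of programmes, so the cost in degrees of freedom and the size of the categories are unknown.
- A reader might infer that leaving these variables out of the ANCOVA weakens the handling of missing weights. The article says only that absent participants will have their final weight imputed. The imputation variables may be set in a fuller plan that is not shown, and variables can enter an imputation model without being in the ANCOVA. No claim is made on that point.

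What survives is narrower. The article does fix the covariate set, it omits two baseline values already held, and adding them costs almost nothing.

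**Conclusion.** The point holds as a suggestion for efficiency. The planned primary analysis is valid and has its stated power, but it leaves unused the starting weight (hence the amount lost) and gender.

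The size of the gain is unknown. Under an assumed further R² of 2% to 10%, the SE falls by about 1% to 5% and power at 2 kg rises by about 0.6 to 2.7 percentage points. At a true difference of 1.5 kg, power would move from 68.4% to between 69.3% and 73.0%. The gain could be close to zero. The case for the change therefore rests on its very low cost, not on a demonstrated benefit.

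**What to change.** Before unblinding, pre-specify the primary and three-month ANCOVA with these terms:

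- trial arm;
- baseline weight;
- the factor actually used to stratify randomisation (intention to continue the programme), worded the same way in the Randomisation and Analysis plan sections;
- pre-programme starting weight or percentage lost (one of the two, since with baseline weight in the model they carry nearly the same information);
- gender.

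Add the initial programme only if it has few, well-filled categories. Report the currently planned model, with baseline weight and the stratification factor only, as a sensitivity analysis.

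The cost is a line or two of wording and, without programme, about two degrees of freedom out of roughly 420 completers (2 × 210). No new data are needed. The sponsor could gauge the likely gain from starting weight in advance, because the pilot SD was computed in people selected on percentage of starting weight lost, so that dataset must hold starting and later weights.

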### Secondary outcomes

The proportion of participants in the intervention and comparator group who have regained less than 1 kg in weight at three and 12 month follow-up.The difference between groups in weight change from baseline to three months follow-up (i.e., end of behavioural support for weight maintenance).The cost to the NHS per kg, and per kg/m [2], of the additional weight loss maintained for the intervention compared to comparator group at 12 months, the cost per quality adjusted life years (QALY) during the intervention period and predicted lifetime QALYs gained.To assess the effects of the intervention on uncontrolled eating, emotional eating and weight preoccupation at three and 12 months follow-up.

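### The successful-maintainer model names only the stratification variable, although the primary analysis of the same weight change also adjusts for baseline weight

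*Protocol article*

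**What the plan says.** The Analysis plan section opens with a general statement: "The analyses will be conducted using the intention to treat principle". For the primary outcome, weight change to 12 months by analysis of covariance, it says: "Thus the analysis uses weight at follow-up adjusted for baseline weight and adjusts for the baseline stratification factor". It describes this as standard practice and applies a similar analysis to the three-month weight change.

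The next paragraph turns to successful maintainers, defined as those who "regain no more than 1 kg from their weight at the end of the weight loss programme", at three and 12 months. The method is "generalised mixed modelling adjusting for the stratification variable", reported as odds ratios with 95% confidence intervals. Baseline weight is not named there. The Secondary outcomes section lists the same endpoint as the proportion "who have regained less than 1 kg in weight at three and 12 month follow-up".

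The Sample size section treats the end of the weight loss programme as the trial baseline, so maintainer status is a threshold on the primary outcome's change score. The Assessments section has a researcher measure weight at the home visit before randomisation, so the covariate exists for every participant.

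**The concern.** Two analyses of one measurement, reported side by side, are specified with different covariates. The continuous analysis removes the part of any between-arm difference that comes from chance imbalance in baseline weight. The binary analysis does not. If the two results diverge somewhat, part of the divergence could come from the covariate sets.

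The 1 kg limit is also the goal that the intervention sets for participants (Intervention components), so this secondary outcome will draw attention. A prognostic covariate that is already measured would give it slightly more power.

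**Working it through.** **1. The plan's own figure.** Inputs from the Sample size section: difference 2 kg, SD 6.3 kg, 90% power, 5% significance (taken as two-sided), 25% loss.

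n per arm = 2 × (1.960 + 1.282)² × 6.3² / 2² = 208.5, so 209. Dividing by 0.75 gives 279 per arm, against 280 stated. The figure reproduces and does not depend on the maintainer model. About 280 × 0.75 = 210 per arm remain at 12 months.

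**2. Maintainer proportions.** The protocol gives no comparator regain, so 3 kg is assumed. With normally distributed change and the cut at 1 kg:

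- Comparator: Φ((1 − 3)/6.3) = Φ(−0.317) = 37.5%
- Intervention: Φ((1 − 1)/6.3) = Φ(0) = 50.0%
- Odds ratio: (0.500/0.500) / (0.375/0.625) = 1.67 (1.66 unrounded)
- Power of a two-proportion comparison at 210 per arm: 73%

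Varying the assumed regain from 1 to 5 kg gives odds ratios of 1.66 to 1.69 and power of 70% to 74%.

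**3. Effect of adding baseline weight.** The correlation between baseline weight and weight change is not in the protocol, so sizes of 0 to 0.4 are assumed; the sign does not affect power. Logistic models were fitted with and without the covariate, once in a large simulated sample (z scaled to 420 participants) and once as repeated trials of 210 per arm.

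| Assumed correlation | Odds ratio without / with | Expected z without / with | Power from repeated trials without / with |
|---|---|---|---|
| 0 | 1.664 / 1.664 | 2.567 / 2.567 | 74% / 74% |
| 0.1 | 1.667 / 1.673 | 2.577 / 2.584 | 74% / 74% |
| 0.2 | 1.663 / 1.685 | 2.563 / 2.596 | 74% / 75% |
| 0.3 | 1.662 / 1.712 | 2.560 / 2.629 | 74% / 77% |
| 0.4 | not run | not run | 74% / 78% |

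Converting z to power by Φ(z − 1.96) gives 72.7% against 73.8% at 0.2, and 72.6% against 74.8% at 0.3. The gains are therefore about 1 and 2 points, in line with the repeated trials within simulation error. No setting shows a material loss.

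These are single-time-point logistic models. They approximate the 12-month comparison and do not reproduce the full mixed model.

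**4. Size of an uncorrected chance imbalance.** At 210 per arm, the standard error of the difference in mean baseline weight is √(2/210) = 0.098 SD. An imbalance of two standard errors is therefore 0.195 SD. It shifts the difference in change by correlation × 0.195 × 6.3 kg:

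- Correlation 0.2: 0.25 kg
- Correlation 0.4: 0.49 kg

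From step 2, 2 kg corresponds to ln(1.66) = 0.507, or about 0.253 per kg. The odds ratio would thus be multiplied or divided by about exp(0.253 × 0.25) = 1.06, or exp(0.253 × 0.49) = 1.13. An imbalance that large is uncommon under randomisation.

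**The case against.** **The starting weight is already in the outcome.** Maintainer status is measured from the end-of-programme weight, so further adjustment may look redundant. This does not stand. The primary outcome is also a change from baseline, and the protocol still adjusts it for baseline weight. Neither subtracting baseline nor cutting the result at 1 kg removes an association between baseline and change.

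**Omitting a covariate is not an error.** This stands. The stratification factor is in the model, randomisation protects the comparison, and the mixed models for the eating and weight-preoccupation outcomes are specified in the same way. Odds ratios are non-collapsible, so adding a covariate changes the quantity estimated slightly. The benefit also depends on a correlation that the protocol does not supply.

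**Stronger readings that the protocol does not support.**

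- A reader might infer that the maintainer model excludes imputed weights and so rests on different people, because the primary analysis is described thus: "All participants will be included in the primary analysis but those who are absent from follow-up will have final weight imputed". The protocol does not say this. It puts the analyses under intention to treat and is silent on missing weights for this outcome. An article commonly leaves that detail to the full analysis plan.
- Nor is it safe to prescribe the same imputed weights here, since no imputation method is named. If baseline weight were carried forward, every absentee would count as a maintainer. With 25% missing per arm, the proportions become 0.25 + 0.75 × 37.5% = 53.1% and 0.25 + 0.75 × 50% = 62.5%. The odds ratio then falls from 1.67 to 1.47, a larger change than anything the covariate produces.
- A reader might treat this as the only outcome that addresses regain. Mean weight change at three and 12 months addresses it as well.

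**Conclusion.** The point holds as a minor improvement. The plan names a narrower covariate set for a dichotomised form of its primary outcome than for the primary outcome itself. The maintainer analysis remains valid, no stated figure is wrong, and the sample size is unaffected.

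Adding baseline weight is worth about 1 power point or less at a correlation of 0.1 to 0.2, and about 2 to 4 points at 0.3 to 0.4. It also removes the effect of a chance baseline imbalance, as the primary analysis already does. These sizes rest on an assumed 3 kg comparator regain, normally distributed change, 210 analysed per arm and the assumed correlations. The SD, the 2 kg effect and the 25% loss are the protocol's.

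**What to change.** In the Analysis plan section, state that the generalised mixed model for maintainer status at three and 12 months adjusts for baseline weight as well as the stratification variable, matching the primary analysis of covariance.

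This takes one line of wording and no new data. The cost is that the odds ratio becomes conditional on one more covariate: in the calculations above it moves from about 1.66 to between 1.66 and 1.71 for correlations up to 0.3. The change should be made before the data are unblinded. It neither requires nor implies any change to how missing weights are handled.

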### Assessments

#### Baseline

A researcher measures participant’s height and weight at a home visit before randomisation. Participants complete the baseline questionnaire and answer the open ended questions about their previous weight loss attempts and strategies they use to control their weight before being randomised. As a process measure the intervention group will be given a set of BodyTrace scales to use to weigh themselves, these scales transmit weight data to a remote database to provide an objective measure of weighing frequency (see below).

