### Process measures

We are collecting process measures to monitor recruitment, intervention delivery and potential variables that may mediate the outcomes. Our hypothesis is that self-weighing leads to the development of conscious cognitive restraint, which the National Weight Control Registry has found to be a key behavioural attribute associated with weight maintenance [17]. Using six items from the revised three factor eating questionnaire [16] we will examine if feedback from self weighing has led to development of conscious cognitive restraint of eating (measured in both groups) at three, six and 12 months post randomisation. In the intervention group we will use seven items from the index of habit strength [18] to measure the automaticity of self-weighing and five items from Steinberg [12] to measure perceptions of daily self weighing at the same follow-ups. At three, six and 12 months follow up participants in both groups will be asked to complete a series of open ended questions about any weight control practices they may have used in the previous two weeks, which will be coded. Within these questions we will specifically ask participants whether they have reapplied any behavioural techniques they acquired through participation in their weight loss programme and whether they have re-enrolled in a weight loss programme. We will then be able to examine whether the intervention may work by encouraging people to reapply lessons and techniques they learnt on the weight loss programme or it works by encouraging participants to enrol in a weight loss programme once more. Table 2 documents the process measures collected.

**Table 2 Tab2:** Measurements and study questionnaires at baseline and follow-ups

Reach		
Number of participants eligible		
Number of participants consented		
Number of participants consented and randomised		
Intervention		
	Comparator group	Intervention group
Frequency of recording self-weighing –record cards		X^a^
Frequency of self-weighing (objective scales)		X
Psychological Measures		
Index of habit strength [18]		X
Energy restriction [16]	X	X
Perceptions of self-weighing [20]		X
Thoughts about regular weighing (open ended questions)		X
Weight locus of control [21]	X	X
Weight loss strategies		
Weight control strategies (including frequency of self-weighing) [22]	X	X
Attendance at commercial weight loss programmes & application of skills learnt at weight loss programme (open ended)	X	X

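### The models for uncontrolled eating, emotional eating and weight preoccupation name the stratification variable but no use of the baseline score, which may cost precision

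*Protocol article*

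**What the plan says.** The Secondary outcomes section of the protocol article includes this aim: "To assess the effects of the intervention on uncontrolled eating, emotional eating and weight preoccupation at three and 12 months follow-up". The Analysis plan gives the model in one sentence: "Groups will be compared with repeated measures mixed modelling, adjusting for stratification variable". Results are to be reported as adjusted means with 95% confidence intervals.

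For the primary outcome the same section names two covariates: "Thus the analysis uses weight at follow-up adjusted for baseline weight and adjusts for the baseline stratification factor". The three-month weight comparison is to be done in a similar way.

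On the availability of baseline scores, the Baseline section under Assessments says, of the period before randomisation: "Participants complete the baseline questionnaire and answer the open ended questions". It does not list the scales. Table 2, under Process measures, is captioned "Measurements and study questionnaires at baseline and follow-ups", but no row names uncontrolled eating, emotional eating or weight preoccupation.

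**The concern.** A person's score on an eating-behaviour or weight-preoccupation scale before randomisation can be expected to predict the later score on that scale. A model that leaves it out treats stable differences between people as noise. The intervals are then wider than the data require, and a chance difference between arms at baseline stays in the point estimate.

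This matters because of what these scales can show. The section on serious adverse events covers only bulimia, anorexia and self-harm that lead to hospital admission. An adverse effect of daily weighing on eating or preoccupation short of admission would show mainly on these scales. If the arms look alike, the width of the interval decides how large an adverse effect can be ruled out.

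**Working it through.** **The plan's own figure.** The article states a sample size only for weight: 280 per arm "will be sufficient to detect a 2 kg difference in change in weight at 12 months follow-up", with 90% power, 5% significance (taken as two-sided), SD 6.3 kg and 25% loss.

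- n per arm = 2 × (1.960 + 1.282)² × 6.3² / 2² = 208.5, so 209.
- 209 / 0.75 = 278.7, so 279 per arm and 558 in total.
- With the t distribution: 210, then 210 / 0.75 = 280 per arm and 560 in total.

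The stated 560 is reproduced. It does not depend on the point made here.

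**Inputs for the psychological scales.** No power or precision is stated for them. I take 210 completers per arm (280 × 0.75), assuming that questionnaire loss equals the 25% allowed for weight. Scores are in SD units. The correlation ρ between baseline and follow-up is not in the article, so a range is assumed.

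**Variance of the arm difference at one follow-up, complete data, large samples.**

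- Follow-up scores only: 2/n.
- Baseline as a covariate, or as a response with a common mean across arms: 2(1 − ρ²)/n.
- Baseline as a response with separate arm means, effect read as difference in change: 4(1 − ρ)/n.

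**Follow-up only against baseline-adjusted.** Without the baseline score the standard error is √(2/210) = 0.0976. The 95% half-width is 1.96 × 0.0976 = 0.191 SD, and the difference detectable with 90% power is 3.242 × 0.0976 = 0.316 SD. With it, each is multiplied by √(1 − ρ²):

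| Assumed ρ | √(1 − ρ²) | Cut in SE | Half-width (SD) | Detectable at 90% power (SD) |
|---|---|---|---|---|
| 0.3 | 0.954 | 5% | 0.182 | 0.302 |
| 0.5 | 0.866 | 13% | 0.166 | 0.274 |
| 0.6 | 0.800 | 20% | 0.153 | 0.253 |
| 0.7 | 0.714 | 29% | 0.137 | 0.226 |

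**The three readings at ρ = 0.6.**

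- Follow-up only: √(2/210) = 0.0976.
- Unconstrained baseline: √(4 × 0.4/210) = 0.0873.
- Covariate or common mean: √(2 × 0.64/210) = 0.0781.

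A simulation of 4,000 trials gave 0.097, 0.088 and 0.078. Moving from the unconstrained reading to the adjusted one gains 1 − 0.0781/0.0873 = 11%. Moving from the common-mean reading gains nothing.

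The unconstrained reading beats follow-up only when 2(1 − ρ) < 1, that is, when ρ is above 0.5. At 0.5 the two are equal (factor 1.0). At 0.3 the unconstrained reading is worse (factor 1.4 against 1).

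**The case against.** A reader might infer that the plan adjusts for stratification alone and throws away a baseline score it has collected. The article does not support that. It neither says that no other covariate is used nor excludes baseline scores. A repeated measures model can carry baseline as one of its responses, in which case it need not appear among the covariates. With a common baseline mean, this loses nothing against covariate adjustment. Reference to three and 12 months makes a follow-up-only model a natural reading, but does not prove it.

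Nor does the article say that these scales are measured at baseline. The Table 2 row on energy restriction cites the three factor eating questionnaire, but it fits the cognitive restraint measure better than these three outcomes.

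It can also be said that this detail belongs in a full analysis plan, which is not shown and may settle it. Any loss is of efficiency: randomisation keeps the unadjusted comparison valid, and its interval already allows for chance imbalance.

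All of this narrows the point. What stands is that the article does state a model and a covariate, states no use of baseline where the weight analysis does, and so permits analyses of different precision.

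The point should not be carried over to cognitive restraint in the Analysis plan for process measures. That analysis is of an association with weighing frequency, not a comparison between arms.

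**Conclusion.** The point holds as a gap in a stated model, worth closing but not critical. Its size depends on two things the article does not give: the baseline-to-follow-up correlation, and how baseline enters the model, if at all. Against a follow-up-only model, the avoidable part of the standard error is modest at a correlation of 0.3 and material from about 0.5. If baseline is already a response with a common mean, there is no loss. All figures assume complete data at one follow-up and 210 completers per arm. The estimated effects would be unbiased on any of the three readings.

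**What to change.** First confirm which of the three scales are in the pre-randomisation questionnaire. For each that is, reword the sentence in the Analysis plan along these lines: *the three- and 12-month scores will be analysed in a repeated measures mixed model with the baseline score of the same scale (or with baseline as a response whose mean is common to both arms), the stratification variable and an arm-by-time term.* Choose one of the two ways of using baseline and fix it before the allocation is revealed to the trial statistician. If the full analysis plan already specifies this, the article's sentence needs only to be aligned with it.

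The cost is one phrase. No new data are needed for a scale already collected at baseline. For a scale not collected then, the present sentence can stand.
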